## Materials and Methods

### Study design

This study is designed as a population-based retrospective cohort study, aiming to emulate a suite of target trials (i.e., hypothetical randomized clinical trials, RCTs) for individuals initiating methadone, buprenorphine/naloxone, or SROM between June 1, 2017, and December 31, 2022, in BC, Canada. This timeline ensures the availability of SROM alongside methadone and buprenorphine/naloxone in BC. Although RCTs are the gold standard for determining comparative effectiveness, they are often time-intensive and may lack generalizability to broader population.[42] By leveraging large-scale health administrative datasets and advanced statistical techniques, observational studies can address many common biases and yield treatment effect estimates based on real-world evidence.[43–46] We will explore the effect variation across key sub-populations which will help identify most beneficiary group from SROM compared to methadone, buprenorphine/naloxone. Key elements of the target trials and their emulations are summarized in Table 1.

This study will utilize population-level data derived from the linkage of nine provincial health administrative databases in BC, where residents are required to participate in a single-payer health insurance system. Using the BC PharmaNet database,[47] which captures daily medication dispensations, we will identify dispensation dates and doses for methadone, buprenorphine/naloxone, and SROM (refer to **S1 Table** for a list of drug/product identification numbers) to define treatment episode. Additional databases include the Discharge Abstract Database[48] (DAD, documenting hospitalizations), Medical Services Plan[49] (MSP, containing physician billing records), BC Vital Statistics [50] (BCVS, capturing deaths and underlying causes), BC Provincial Corrections [51] (recording incarceration entries and releases), Perinatal Care Database[52] (PSBC, covering maternal and infant outcomes), National Ambulatory Care Reporting System[53] (NACRS, documenting Emergency Department visits), Client Roster[54] (providing demographic and geographic data), and the BC Social Development and Poverty Reduction database[55] (tracking social assistance). These datasets are linked at the individual level using a de-identified personal health number assigned by the BC Ministry of Health.[56] A description of these databases and the timeline for data extraction is detailed in **S2 Table**.

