### Study follow-up

The time zero is the first dispensation date of methadone, buprenorphine/naloxone, or SROM. For initiator analysis, follow-up ends at the earliest of outcome, death, loss to follow-up, 24 months after time zero, or December 31, 2022. For per-protocol analysis, we will censor at additional events: (i) treatment switch or falls OAT dose below the key benchmark, and (ii) individuals initiate taper or violate eligibility criteria, such as being pregnant, or incarcerated, or had received cancer or palliative care (see Table 3).

However, for sub-populations (ix) and (x), where treatment is considered a time-varying exposure and individuals may be consistent with both treatment strategies up to 30 days of OAT episode, we will apply the ‘clone-censor-weight’ approach to emulate the per-protocol target trial.[59,60] In this approach, each individual will be replicated into two clones, one for each treatment strategy. When individuals are no longer consistent with the assigned strategy due to a treatment switch, taper initiation, or violation of eligibility, we will artificially censor the corresponding clone at that time. For the clone assigned to the switch to SROM group, individuals will remain uncensored if they switch to SROM within 30 days of OAT episode, and be censored at day 30 if they have not switched by then (see Table 3).

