### Statistical analysis

We will adjust for all baseline covariates to estimate the initiator effect as hazard ratios, differences of cumulative incidence (risk) at 24 month, and risk curves using a marginal structural Cox proportional hazard regression model (MSM) with inverse probability of treatment weighting.[71,72]. For the per-protocol analysis, additional time varying confounding will be adjusted via censoring weights to mitigate selection bias from artificial censoring due to receipt of dose below key benchmark, treatment switching, violation of eligibility criteria including initiating pregnancy, incarceration, or treatment taper. However in the ‘clone-censor-weight’ approach for the sub-population (ix) and (x), we will not artificially censor for the violation of dosing benchmark and will estimate the artificial censoring weights conditional on their covariate history. Sandwich variance estimates will be used to compute the 95% compatibility (confidence) intervals for the adjusted hazard ratios,[73] while 500 bootstrap samples (with replacement) would be used to compute the compatibility intervals for risk differences and compatibility curves for risk curves.[74] We will apply high-dimensional propensity score (hdPS) and instrumental variable (IV) approaches for the initiator analysis as sensitivity analyses.[75,76] While the MSM and ‘clone-censor-weight’ approaches will target the marginal treatment effect, the IV analysis will estimate a local average treatment effect among compliers, i.e., individuals who would be prescribed the treatment preferred by treating physician or facility (see details in IV estimation section later). We will use SAS version 9.4 to prepare analytic data and conduct the statistical analysis using the SAS and R version 4.5.0.

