### Initiator analysis

We will apply a multinomial logistic model to estimate the probability of initiating SROM, methadone or buprenorphine/naloxone, incorporating selected baseline covariates, to adjust for confounding by indication at time zero. The treatment weights will be estimated by taking the inverse of the probability of initiating the observed form of OAT. The selection bias induced by censoring due to death or loss to follow-up will be controlled via censoring weights estimated from a pooled logistic regression model.^67^ To estimate weekly censoring weights, the model will incorporate an indicator for week (modelled with cubic splines), product of week and medication, and both time-fixed and time-varying covariates ().

$$SW_{it}=\prod_{j=1}^{t}\frac{\mathrm{Pr}.(C_{ij}=0|L_{i0},{\bar{C}}_{i,j-1}=0)}{\mathrm{Pr}.(C_{ij}=0|L_{i0},{\bar{L}}_{ij},{\bar{C}}_{i,j-1}=0)},$$

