where $SW_{it}$ is the stabilized weight for the *i*th individual at time t, $C_{ij}$ is the censoring status for the *i*th individual at *j*th time, ${\bar{C}}_{ij}$ is the censoring history for the *i*th individual at *j*th time, $L_{i0}$ is the list of time-fixed covariates including treatment arm, ${\bar{L}}_{ij}$ is the time-dependent covariate history for the *i*th individual at *j*th time. Time-dependent covariates will be lagged by one week to ensure censoring is predicted using prior-week covariates. Same set of baseline and time-varying covariates will be included in the treatment and censoring models. Both treatment weights at time zero and censoring weights will be stabilized, truncated at the 99th percentile to limit the influence of extreme values and their product will be used as the final weights.[72] Covariate balance will be assessed using standardized mean differences (SMD), with SMD <0.10 considered balanced.[77] To fit the marginal structural model, a pooled weighted logistic regression model will be fitted to compare the time to OAT discontinuation, all-cause mortality, and overdose-related acute care visits across treatment groups. Based on the fitted models, individual time-to-event (survival) probabilities will be predicted weekly for each treatment arm by setting the treatment equal to a specific value (e.g., SROM, methadone, or buprenorphine/naloxone) for all individuals. These predicted probabilities will then be averaged across the population to get week-specific survival probabilities. The risk of the events will be estimated as one minus the averaged survival probability, with risk differences calculated for SROM initiators versus buprenorphine/naloxone and methadone. We will report hazard ratios, risk differences, and risk curves. Compatibility intervals and curves will be computed using the approach described in the Statistical analysis section.

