### Per-protocol analysis

We will conduct a per-protocol analysis to estimate treatment effects under sustained adherence at key dosing benchmarks, complementing the initiator effect.[86] To control the selection bias due to artificial censoring, we will consider two censoring models along with the propensity score models: (i) accounting for treatment switching, receipt of dose below key benchmark, and (ii) accounting for death, loss to follow-up, protocol violation by initiating pregnancy, dose taper, incarceration, or receipt of cancer or palliative care (see Table 3 for outcome specific censoring mechanism). Dose tapering is defined as two consecutive daily dose reductions without an intervening increase. Both censoring weights will be estimated using the approach described in the Initiator analysis section earlier. Final weights will be the product of the stabilized inverse probability of treatment weights at time zero and the post-baseline inverse probability of censoring weights, truncated at the 99th percentile. In the marginal structural model, we will apply a pooled logistic regression approach incorporating the final weights. The fitted model will be used to compute hazard ratios, risk differences, and risk curves. Compatibility intervals and curves will be computed using the approach described earlier. For sub-populations (ix) and (x), the censor-weighting approach will be similar, but we will apply a modified censoring mechanism as described in Table 3.

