Treatment switch		C_3_		C_3_		C_3_
The overdose-related first acute-care visit					outcome	outcome

a. end of study follow-up is either Dec 2022 or 24 months from time zero, whichever occurs earlier C_1_, C_2_, and C_3_ indicate different censoring mechanism: C_1_: censoring due to end of study follow-up; C_2_: censoring due to death (not the all-cause mortality outcome), loss to follow-up, deviation from the trial exclusion criteria such as initiation of pregnancy, incarceration, dose taper, cancer or palliative care, leaving out of BC. Dose taper will be defined as two consecutive daily dose decreases (without intervening increase); C_3_: censoring due to deviation from the dosing protocol as mentioned in the key measures section, including treatment switching. Censoring for violating dosing protocols will not be applied to the study sub-populations (ix) and (x), as defined in Table 2. For the clone designated for switching to SROM in these sub-populations, individuals will be censored at day 30 if they remain on the initial OAT beyond 30 days, but will not be censored if they switch to SROM within 30 days of initiation; Separate censoring models will be used for C_2_ and C_3_.

**Table 4. T4:** Time fixed and time-varying covariates to estimate the inverse probability of treatment and censoring weights

Variable	Category	How the variable is defined and measured
*Socio-demographic factors*		
Age	Continuous	Based on birth date information from the client registry.
Sex	Male/Female	Based on medical records that record sex.
Living in rural region	Yes/No	Based on the population of the assigned local health area[65]
Homelessness/unstable housing in past 5 years^‡^	Past year, Past 1–5 years, Never/>5 years	Defined through International Classification of Diseases (ICD) 10: Z59.0, Z59.1 from physician billing or hospital discharge records or 3 consecutive records of no fixed address from Social Development and Poverty Reduction (SDPR)
Incarcerated in past year^‡^	Yes/No	Admission to BC correctional facilities and identified through records in the past year from the provincial corrections database.
Receipt of income assistance in the past year^‡^	Yes/No	Identified through records in SDPR and PharmaCare plan information on medication dispensations, using records within the past year.
Calendar year of time zero	2010 to 2022	Determined based on the dispensation date from PharmaNet.
*Comorbidity*		

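### Death is censored and weighted for discontinuation and overdose visits, so the 24-month risks assume no deaths and are not cumulative incidence; overdose deaths without a coded visit are missed

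*Protocol article*

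**What the plan says.** Under Study follow-up, the initiator analysis has one stopping rule for all outcomes: "follow-up ends at the earliest of outcome, death, loss to follow-up, 24 months after time zero, or December 31, 2022". Table 3 codes death as C2 for OAT discontinuation and for overdose visits, in both the initiator and the per-protocol columns. Death is an outcome only in the all-cause mortality columns. The footnote describes C2 as "censoring due to death (not the all-cause mortality outcome), loss to follow-up", followed by the eligibility deviations.

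The Initiator analysis section states the handling: "The selection bias induced by censoring due to death or loss to follow-up will be controlled via censoring weights". The Per-protocol analysis section uses a single model for this group, "accounting for death, loss to follow-up, protocol violation by initiating pregnancy, dose taper, incarceration, or receipt of cancer or palliative care". On the estimator the plan says: "The risk of the events will be estimated as one minus the averaged survival probability". The Statistical analysis section names the result "differences of cumulative incidence (risk) at 24 month". Table 1, in its analysis-plan row for populations (i) to (viii), mentions initiator censoring weights for loss to follow-up and does not mention death.

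Key measures defines the overdose outcome as an acute care visit coded T40, T42.4 or T43.6. The composite in Table 5 joins that visit with OAT discontinuation. Neither includes fatal overdose. Study design describes BC Vital Statistics as "capturing deaths and underlying causes".

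**The concern.** Loss to follow-up hides an event that may still happen. Death prevents it. If death is censored and the survivors are upweighted, the estimate describes a population in which nobody dies before the event. That can be a legitimate target, but the plan does not declare it and gives it the name of a different quantity. Discontinuation, one of the two affected outcomes, is a primary outcome.

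The second issue concerns the overdose outcome. A person who dies of an overdose without reaching acute care has had the most serious form of the event that this outcome is meant to reflect, yet contributes no event to it. If mortality differs between arms, the omission is differential. The protocol's Introduction raises that possibility itself: it cites a French cohort with 9.1-fold and 3.9-fold higher mortality incidence on SROM than on buprenorphine and methadone, and notes potential selection bias in that cohort. The protocol figure therefore shows that a difference is plausible. It is not an expected effect in this study.

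**Working it through.** **No figure to reproduce.** The document gives no event rate, death rate, event count or sample size. All rates below are assumptions, used only to show direction and order of size.

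**Set-up.** Constant hazards over T = 2 years. Let l be the event hazard, m the death hazard, and f the part of m due to overdose deaths without a coded visit (share s, so f = s × m).

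- Planned estimator, death censored: 1 − exp(−l·T)
- Cumulative incidence, death competing: l/(l+m) × [1 − exp(−(l+m)·T)]
- Visit or unattended overdose death, other deaths competing: (l+f)/(l+m) × [1 − exp(−(l+m)·T)]

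**Step 1: the label.** Overdose visits at l = 0.10 per year: the planned risk is 1 − exp(−0.20) = 18.13% whatever the death rate.

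| m per year | Planned | Cumulative incidence |
|---|---|---|
| 0.01 | 18.13% | 17.95% |
| 0.02 | 18.13% | 17.78% |
| 0.05 | 18.13% | 17.28% |

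Over l = 0.05 to 0.20 and m = 0.01 to 0.05 the gap is 0.1 to 1.5 points. For discontinuation at l = 1.5 the planned risk is 95.02%, against 94.49%, 93.96% and 92.41% at the same three death rates. Over l = 0.7 to 3.0 the gap is 0.3 to 2.8 points. The mislabelling is real but modest in size.

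**Step 2: unattended overdose deaths, equal visit hazards.** Two arms with l = 0.10 and m = 0.04 v 0.02. The planned difference is 0.00 points. For s = 50%: higher-mortality arm 0.12/0.14 × (1 − exp(−0.28)) = 20.93%; other arm 0.11/0.12 × (1 − exp(−0.24)) = 19.56%.

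| Share s | m = 0.04 | m = 0.02 | Difference |
|---|---|---|---|
| 10% | 18.14% | 18.14% | 0.0 |
| 25% | 19.19% | 18.67% | +0.52 |
| 50% | 20.93% | 19.56% | +1.37 |
| 75% | 22.68% | 20.45% | +2.23 |

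**Step 3: can the sign change?** Visit hazards 0.09 v 0.10, same death rates. The planned difference is 16.47% − 18.13% = −1.65 points (from unrounded values). Counting unattended overdose deaths gives −1.06, −0.19 and +0.69 points at s = 25%, 50% and 75%. The sign reverses at the largest share.

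**Step 4: is a competing-event estimator enough?** No. In Step 2, cumulative incidence of visits alone gives 17.44% v 17.78%, a difference of −0.34, so the higher-mortality arm looks slightly better. Discontinuation behaves the same way: at l = 1.5 it is 92.93% v 93.96%, or −1.04 points. In an extreme case (cumulative death hazards 0.18 v 0.02 over 24 months, net discontinuation risk 95%) it is 90.4% v 94.5%. People who die on treatment count as never having discontinued.

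**The case against.** A reader might infer that fatal overdoses are scored as non-events and that deaths vanish from the study. The documents do not support that:

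- A fatal overdose with a T40, T42.4 or T43.6 acute care visit is an event. Only one without a recorded visit is missed, and the documents do not give that share.
- A censored death is not treated as event-free. Its remaining follow-up is represented by upweighted survivors of the same arm with similar covariate history.
- The omission comes mainly from the outcome definition, not from C2. Step 4 shows that changing the estimator alone would not recover these deaths.
- All-cause mortality is named as a primary outcome in the Abstract and Key measures, with its own hazard ratios, risk differences and curves. An arm with more deaths shows it there.

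A reader might also carry the 9.1-fold ratio over into a large bias here. The cited comparison comes from a relatively small cohort of SROM users that the protocol itself flags for potential selection bias, so it cannot stand in for the weighted contrast in this study.

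It can fairly be added that risk under elimination of death is a recognised estimand, and that the Discussion already lists overdoses without medical attendance as incompletely captured. Both points stand. Neither removes the wrong label or the conflict with Table 1, and the stated limitation leaves unused a data source that the study has already linked.

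**Conclusion.** The concern holds in a limited form. As written, the discontinuation and overdose-visit risks are risks under hypothetical elimination of death, not cumulative incidence. Table 1 disagrees with Table 3 and the Initiator analysis section on whether death enters the censoring weights. The mislabelling alone is worth about 0.1 to 1.5 points for overdose visits and 0.3 to 2.8 points for discontinuation under the assumed rates.

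The more consequential gap is that overdose deaths without a coded visit are absent from both the overdose outcome and the Table 5 composite. With death rates of 0.04 v 0.02 per year and 25 to 75% of deaths of this kind, the risk difference shifts by about 0.5 to 2.2 points when visit hazards are equal, and by up to 2.3 points in the unequal case (−1.65 to +0.69), where the sign can reverse. At a 10% share the shift is close to nil. These sizes rest wholly on assumed constant hazards, an assumed mortality difference and an assumed share. The direction needs only higher mortality in one arm and a share that is not small.

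**What to change.** 1. Define the overdose outcome as an overdose acute care visit or an overdose death, using underlying cause from BC Vital Statistics. At the least, add this as a pre-specified analysis beside the visit-only outcome.
2. Report discontinuation-or-death alongside discontinuation, so that deaths on treatment count against retention somewhere.
3. Choose one of two routes for the non-mortality outcomes. Either keep the death-censored analysis, state that the risks apply under elimination of death, and drop the cumulative incidence label. Or estimate cumulative incidence with death as a competing event and take death out of the censoring weights: the initiator weights then cover loss to follow-up only, and the other per-protocol censoring reasons stay. If the second route is taken, always present it beside the mortality result, because the higher-mortality arm will otherwise look better.
4. Reconcile the analysis-plan row of Table 1 with Table 3 and the Initiator analysis section.

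The cost is small: outcome code, some wording and two further sets of estimates from data already linked, with no analyses yet run according to Study status and timeline. The main drawback is that cause-of-death coding for late-2022 deaths may be incomplete, which should be checked before the outcome is fixed.

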### Covariate selection

We propose to include all selected confounders identified in a recent methadone versus buprenorphine/naloxone study,[61] which applied a modified disjunctive cause criterion[62] to the augmented list of covariates from systematic reviews.[63,64] These covariates include socio-demographic factors, measures of disease severity and comorbidity, and OAT-related factors. Additionally, COVID-19-related covariates will be included to control potential selection bias introduced by pandemic-related service disruptions and differential treatment accessibility (see Table 4 for the list of covariates).

All time-varying covariates will be updated weekly. These covariates will be used to estimate the inverse probability of treatment as well as censoring weights to adjust for measured confounding and informative censoring respectively.

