### IV estimation

We will apply IV estimation for initiator analysis as a sensitivity method to address potential uncontrolled confounding. Given the lack of established IV methods for multi-category exposures in time-to-event analyses, we will define a binary exposure: SROM versus either methadone or buprenorphine/naloxone. Two candidate IVs will be tested: (a) prescriber-level preference for SROM and (b) facility-level preference for SROM, both measured among OAT clients in the six months prior to time zero.[80] The validity of the IV relies on four key assumptions. First, the relevance assumption will be tested using a logistic regression model to assess the association between the IVs and the exposure while adjusting for individual- and prescriber-level characteristics. The exclusion restriction and exchangeability cannot be directly verified, so their plausibility will be assessed through expert clinical input from our scientific advisory committee. Additionally, we will evaluate bias due to omitted measured covariates by comparing non-IV and IV analyses.[81] The assumption of homogeneity defines whether the IV-exposure association remains consistent across measured confounders of the exposure-outcome association.[82] The monotonicity assumption requires that there are no “defiers”, i.e., individuals who would always receive opposite treatment to that assigned by IV, and is expected to hold trivially in this context since OAT initiation with SROM is largely determined by prescriber or facility preference rather than individual choice. Since homogeneity and monotonicity cannot be empirically tested, their validity will be assessed through expert consultation.[80,83] To estimate the local average treatment effect, we will apply a two-stage residual inclusion (2SRI) approach.[84,85] In the first stage, a logistic regression approach will model the exposure as a function of the IV and selected covariates, generating residuals that account for uncontrolled confounding. These residuals will be incorporated into a Cox-PH model alongside the exposure and selected covariates. From this fitted model, we will estimate hazard ratios, risk differences, and risk curves. Compatibility intervals and curves will be computed using the approach described earlier.

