**Sample restriction**		
PWOUD with chronic pain.	To evaluate treatment effect variability in populations prioritized by The American Society of Addiction Medicine national practice guidelines.[87]	Both
Adolescents.		Both
Individuals in the criminal justice system.		Both
PWOUD with mental health disorders. ^a^		Both
PWOUD with history of prescription opioid prior to OUD diagnosis.	To evaluate the robustness of treatment effects among individuals who primarily misuse PO.	Both
PWOUD in regions with highest fentanyl concentrations. ^b^	To understand the robustness of treatment effects in areas where illicit fentanyl use is most prevalent.	Both
PWOUD receiving care in Community Health Centres. ^c^	To evaluate heterogeneity of treatment association across clinical settings.	Both
PWOUD receiving care in stand-alone physician practices. ^d^		Both
Excluding PWOUD receiving OAT by primarily detox prescribers. ^e^	To evaluate the robustness of treatment effect by removing individuals receiving OAT for rapid detoxication.	Both
Excluding OAT episode initiating right after hospital discharge.	To evaluate the treatment association among OAT episodes with its first dose dispensed at community pharmacy.	Both
Excluding PWOUD with indication of heart failure or cardiomyopathy.	To remove individuals with pre-existing risk of prolonged QT interval, which is a caution for initiating methadone	Both

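### Place enters the planned weights only as rural yes/no, so regional differences in drug supply and SROM uptake may leave residual confounding in the mortality and overdose comparisons and in the preference-based IV analysis

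*Protocol article*

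**What the plan says.** Table 4 of the protocol article is the covariate list for the weights. The Covariate selection section states: "These covariates will be used to estimate the inverse probability of treatment as well as censoring weights". The Initiator analysis section adds: "Same set of baseline and time-varying covariates will be included in the treatment and censoring models".

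Table 4 has one variable for place, "Living in rural region", coded yes/no and defined as "Based on the population of the assigned local health area". Finer geography is held, because the local health area is needed to build the flag and the Study design section describes the linked Client Roster as "providing demographic and geographic data".

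Three other statements bear on whether region matters:

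- The IV estimation section says "OAT initiation with SROM is largely determined by prescriber or facility preference rather than individual choice" and takes prescriber-level and facility-level preference as the candidate instruments.
- The Introduction (Adapting clinical guidelines to a new drug landscape) connects fentanyl with rising overdose risk and with a possible need for higher treatment doses.
- Table 5 plans a restricted analysis of "PWOUD in regions with highest fentanyl concentrations", with the rationale "To understand the robustness of treatment effects in areas where illicit fentanyl use is most prevalent".

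**The concern.** A covariate must be balanced if it influences both which drug is started and the outcome. The plan supplies most of the argument that region does both. Prescribers and facilities sit in particular places, so if their preference largely decides who starts SROM, SROM uptake can differ by place. If fentanyl raises overdose risk and its concentration differs between regions, death and overdose risk can differ by place too. A rural flag does not separate two non-rural areas that differ on both counts.

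The IV analysis is planned as a check on uncontrolled confounding. If region is a common cause of a facility's preference for SROM and of the outcome in its clients, exchangeability of the instrument fails. The check would then share a gap with the analysis it is meant to test.

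At stake are the comparisons of all-cause mortality (a primary outcome) and overdose-related acute care visits (secondary), which the Discussion says will inform treatment guidelines.

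**Working it through.** The plan gives no figure on this point, so there is none to reproduce. The check is a reading of the covariate lists, followed by an illustration with assumed inputs.

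**1. Which models carry a regional term?**

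- Treatment and censoring weights: the rural flag only. Practice size, prescriber funding, attachment to the prescriber, virtual care, pharmacy delivery and calendar year are not measures of place or drug supply.
- hdPS: proxies come from hospital diagnosis and procedure codes, physician diagnosis and fee codes, and drug class codes. None is geographic.
- IV: the relevance test adjusts for characteristics of the individual and the prescriber, and the two-stage residual inclusion (2SRI) models use selected covariates. No area term is named.
- Table 5 restriction to high-fentanyl regions: it narrows regional variation within a subset but does not adjust the province-wide estimate, and it is not tied to the IV analysis.
- Limitations in the Discussion: regional drug supply is not mentioned.

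**2. Illustration for the main analysis.** All inputs are assumed. Let p1 and p0 be the shares of SROM and comparator starters in high-toxicity areas that remain after weighting on Table 4, and R the outcome ratio between high- and low-toxicity areas. With no true drug effect,

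spurious risk ratio = [1 + p1(R − 1)] / [1 + p0(R − 1)].

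With p0 = 0.40:

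| p1 | R = 1.2 | R = 1.5 | R = 2.0 |
|---|---|---|---|
| 0.40 | 1.000 | 1.000 | 1.000 |
| 0.50 | 1.019 | 1.042 | 1.071 |
| 0.60 | 1.037 | 1.083 | 1.143 |
| 0.70 | 1.056 | 1.125 | 1.214 |

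The smallest non-null value is 1.10/1.08 = 1.019 and the largest is 1.70/1.40 = 1.214. If region is balanced, p1 = p0 and the ratio is 1.00 for any R, provided the region variable captures the toxicity difference.

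**3. Illustration for the IV analysis.** Again all inputs are assumed. On the risk scale, for a simple ratio (Wald) estimator,

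bias = (regional risk difference) × (difference in regional mix between instrument levels) / (first-stage difference in SROM use).

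- Low end: 0.01 × 0.10 / 0.40 = 0.0025, or 0.25 percentage points.
- High end: 0.02 × 0.30 / 0.10 = 0.06, or 6 percentage points.

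The plan uses 2SRI with a Cox model, so these values show the mechanism and do not predict its estimate. A weak first stage magnifies any regional imbalance.

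**The case against.** The strongest case against has five parts.

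- **The causal chain is partly inferred.** The sentence on prescriber and facility preference is there to defend monotonicity and says nothing about geography. The Table 5 rationale concerns robustness of effects and gives no regional mortality contrast. The document reports no SROM share by region. This stands: it limits the point to what may happen.
- **Regional contrast may be small.** The Introduction reports fentanyl in over 80% of unregulated drug deaths in the province by 2017, and the Subgroup and sensitivity analyses section calls it dominant by then. This may shrink the bias. It does not make concentration uniform, and the plan's own restriction presumes that differences remain.
- **Other covariates may act as proxies.** Homelessness, income assistance, incarceration, practice size, prescriber funding and safer supply may vary by area and absorb part of the imbalance. A reader might infer that non-rural areas are treated as identical; they are not. The bias at issue is what remains after these covariates.
- **The IV covariates are not listed in full.** Prescriber characteristics could include practice location. This stands, so the IV statement holds only as far as terms are named. A reader might also infer that the IV bias runs in the same direction as the main one; nothing in the document establishes that.
- **Covariates were chosen by a stated method.** The plan takes them from an earlier study that used a modified disjunctive cause criterion. Whether finer region was considered there cannot be seen, but the printed list fixes place as a binary flag.

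It might also be said that the Table 5 restriction covers a single area. The row speaks of regions in the plural, and the surviving footnotes do not match the row letters, so that cannot be concluded.

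**Conclusion.** The point holds as a risk of residual confounding. Place is fixed as rural yes/no in the treatment and censoring weights, the hdPS sources add no geography, and no area term is named for the IV models. On the plan's own premises, region is a credible common cause of SROM initiation (or of the instrument) and of death and overdose.

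A reader might infer that the comparisons are confounded. The document does not support that, because it gives neither SROM uptake nor outcome risk by region; size and direction are unknown. The range of about 1.02 to 1.21 rests wholly on the assumed imbalances and ratios and falls to 1.00 if SROM share does not vary by region. It illustrates mortality and overdose; nothing was calculated for treatment discontinuation.

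The change should still be made. The data are linked, the Study status and timeline section says no analyses have been run, and the term can be pre-specified now.

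**What to change.** - Add health authority, or local health areas grouped to workable size, as a baseline covariate in the treatment model, the censoring models, the investigator-selected set for hdPS and both 2SRI stages. In sub-populations (ix) and (x), where switching is handled by artificial censoring, the censoring models are where it has to enter.
- Report standardized mean differences for region against the plan's own threshold of 0.10, and report the balance of each instrument by region.
- Add a region-by-calendar-period term only where sub-population size and overlap allow. Elsewhere, run it as a sensitivity analysis. Required in every model, such products could strain the three-arm multinomial model in the smaller sub-populations.

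Cost: a few model terms from data already held, slightly less overlap in small regions, and a somewhat weaker facility-level instrument. Health authority may be too coarse to capture local differences in drug supply, so some regional confounding could remain and should be listed among the limitations.
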